#### D. Stopping rules

No formal stopping rules will be established in advance for efficacy. The trial will be stopped only if the physician monitor believes there is an unacceptable risk of serious adverse events in one or more of the treatment arms. In this case, the physician monitor could recommend terminating one of the arms of the trial or the entire trial.

### Statistical issues

#### A. Sample size and the detectable difference

Because patient function (or dysfunction) is generally considered the more consequential of our two primary outcome measures [27] (the other being bothersomeness of back pain), sample size calculations are based on the Roland-Morris Disability Questionnaire (RDQ). Our sample size is designed to ensure that we have good power to detect a clinically significant difference of 2.5 points for pairwise comparisons (yoga to self care and yoga to exercise) on the RDQ (Aim 1 and 2) and adequate power to detect a difference of 1.7 points between the yoga and exercise groups that would be of interest when exploring mechanisms of action (Aim 3). We think that a smaller detectable difference between yoga and exercise can be justified when examining mechanisms of action because in the Aim 3 comparison of yoga and exercise, we focus on the *additional *benefits of yoga compared with exercise, anticipating that a portion of yoga's clinical effects would actually result from movement.

We have accommodated these dual power needs by proposing a 2:2:1 randomization ratio (yoga: exercise: self care), with a total of 210 participants. Assuming 10% loss to follow-up (which is slightly higher than in our previous study [19]), there would be outcomes data for 75:75:38 participants in the yoga, exercise, and self care groups, respectively. To protect against multiple comparisons, we will use Fisher's protected least significant difference approach, which has been shown to have desirable properties when there are three groups [51]. This approach makes pair-wise comparisons between the three treatment groups only if the overall *F*-test is significant. The power of this omnibus *F*-test depends on how the means from the three treatment groups differ. We therefore assumed that the yoga group would be 1.7 RDQ points superior to the exercise group, which would, in turn, be 0.8 RDQ points better than the self care group (giving a difference of 2.5 points between the yoga and self care groups). We chose a 1.7-point difference between yoga and exercise because it is slightly more conservative (i.e., smaller) than that found in our previous study [19].

Our estimates of the standard deviations of our primary outcome measures adjusted for pre-randomization baseline values were derived from analyses of covariance of 12-week follow-up data estimated from the 101 study participants in our 3-arm pilot study: RDQ standard deviation (SD) = 3.68 and bothersomeness SD = 2.38. With our proposed sample size, the omnibus *F*-test for the RDQ score will have 92% power for detecting a statistically significant difference among the three treatment means with the distribution assumed above. If this omnibus test isstatistically significant we will address Aims 1 and 2 of the study by comparing the appropriate pairs of means, as discussed below. To detect a pair-wise difference of 2.5 RDQ points, we will have 92% power for the yoga (or exercise) to self care comparison and 98% power for the yoga to exercise comparison. For Aim 3 we will have 92% to detect a pairwise difference of 2.5 RDQ points between yoga (or exercise) and self care and 80% power to detect a pairwise difference of 1.7 points between yoga and exercise.

Our sample size will also provide adequate power to detect a clinically important difference of 1.5 on our 0 to 10 bothersomeness measure. For the omnibus *F*-test, we will have 89% power for detecting a significant difference of 1.5 points among the three groups (if we assume a difference of 1.1 points between the yoga and exercise groups and of 0.4 points between exercise and self care). For a difference of 1.5 points on the bothersomeness measure, we will have 88% power for the yoga (or exercise) to self care comparison and 97% power to for the yoga to exercise comparison. For Aim 3, we will have 88% power to detect a pairwise difference of 1.5 bothersomeness points between yoga (or exercise) and self care and 80% power to detect a pairwise difference of 1.1 points between yoga and exercise.

At each time point, both primary outcomes (function and symptoms) will be tested at the 0.05 level because they address separate scientific questions. Analyses of both outcomes at all follow-up times will be reported, imposing a more stringent requirement than simply reporting a sole significant outcome. Arguments against adjusting for multiple comparisons in this situation have been made by Rothman [52,53] and others [54].

The power calculations are based on simple comparisons of the follow-up scores at a single point in time with adjustment for baseline values using analysis of covariance. We also plan to adjust for other baseline characteristics (e.g., age, gender, and baseline covariates found predictive of 10-week outcomes). Inclusion of such baseline covariates can improve precision of the variance estimate and therefore increase power.

Since assessment of Aim 3, the mediator analysis, is dependent on the results from Aim 1 and Aim 2, the study was not directly powered for Aim 3. We ran a simple power analyses for the primary mediator of interest, body awareness, assuming the expected sample sizes of 75:75:38, a single time point, and the RDQ Score as the outcome. We found a median power of 0.86 to detect body awareness as a significant mediator for yoga compared to self care and a median power of 0.83 for to detect body awareness as a significant mediator for yoga compared to exercise.

In summary, we have excellent power to detect a clinically meaningful difference on the omnibus test and the pairwise comparisons with self care for Aims 1 and 2 as well as adequate power to evaluate the yoga - exercise comparison for the mediator analysis for Aim 3. Although powered to detect a clinically significant difference on the RDQ, the resultant sample sizes will provide ample power for both of our primary outcome measures.

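### The 92% and 88% powers quoted for yoga versus self care leave out the omnibus F-test that must be passed first; at the plan's own assumed means the procedure has about 90% and 85%

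*Protocol article*

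**What the plan says.** All the design figures are in the protocol article, Statistical issues, section A (Sample size and the detectable difference).

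- **Gate.** Multiplicity among the three arms is handled by Fisher's protected least significant difference: "This approach makes pair-wise comparisons between the three treatment groups only if the overall" F-test is significant. Section B (Statistical analysis) applies the same condition at each follow-up time before Aims 1 and 2 are tested.
- **Assumed means.** On the RDQ, yoga is 1.7 points better than exercise and exercise 0.8 better than self care (2.5 in total). On bothersomeness the steps are 1.1 and 0.4 (1.5 in total).
- **Omnibus power.** 92% for the RDQ and 89% for bothersomeness.
- **Pairwise power for Aim 1.** "To detect a pair-wise difference of 2.5 RDQ points, we will have 92% power for the yoga (or exercise) to self care comparison". For 1.5 points on bothersomeness, "we will have 88% power for the yoga (or exercise) to self care comparison".
- **Summary claim.** The section concludes that "we have excellent power to detect a clinically meaningful difference on the omnibus test and the pairwise comparisons with self care".

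The section gives omnibus power and pairwise power separately. It never gives the probability that both tests are significant, and it does not say that the pairwise figures leave the gate out.

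**The concern.** Under the plan's procedure, Aim 1 succeeds on an outcome at a given time only if two things happen together: the omnibus test is significant and the yoga versus self care test is significant. The power of the procedure is the probability of that joint event. It cannot exceed either component, and it falls below the pairwise power whenever the omnibus test can miss in a trial where the pairwise test would have been significant.

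Such misses occur because the omnibus test spreads its evidence over two degrees of freedom. A yoga versus self care difference only just past its own critical value can fail the omnibus test when the exercise mean adds little to the spread among the arms.

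What is at stake is the accuracy of the power quoted for the main effectiveness question, not the validity of the analysis.

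**Working it through.** **Inputs** (all from section A)

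- Allocation and size: "proposing a 2:2:1 randomization ratio (yoga: exercise: self care), with a total of 210 participants", so 84:84:42 randomized.
- "Assuming 10% loss to follow-up": 84 × 0.9 = 75.6 and 42 × 0.9 = 37.8. The plan uses 75:75:38, 188 in all, so the residual degrees of freedom are 188 − 3 = 185.
- Baseline-adjusted SD: 3.68 (RDQ), 2.38 (bothersomeness).
- Level: "both primary outcomes (function and symptoms) will be tested at the 0.05 level". Sidedness is not stated. Two-sided is assumed, and it reproduces the stated powers to within about 1 point.
- Means, with yoga at 0 and higher being worse: RDQ 0, 1.7, 2.5; bothersomeness 0, 1.1, 1.5.

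**Step 1: reproduce the stated pairwise powers without the gate**

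Standard error = SD × √(1/75 + 1/38) = SD × 0.1991. Approximate power = Φ(difference / standard error − 1.96).

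- RDQ: 3.68 × 0.1991 = 0.733; 2.5 / 0.733 = 3.41; Φ(1.45) = 92.7%. The noncentral t gives 92.3%. Stated: 92%.
- Bothersomeness: 2.38 × 0.1991 = 0.474; 1.5 / 0.474 = 3.17; Φ(1.21) = 88.6% with unrounded terms. The noncentral t gives 88.1%. Stated: 88%.

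The stated figures are therefore the powers of stand-alone two-sample tests.

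**Step 2: reproduce the omnibus powers**

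Noncentrality λ = Σ nᵢ(μᵢ − μ̄)² / SD², with μ̄ weighted by arm size.

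- RDQ: μ̄ = (75 × 1.7 + 38 × 2.5) / 188 = 1.184; λ = (105.05 + 20.01 + 65.86) / 13.54 = 14.10. Power from the noncentral F on 2 and 185 df is 92.6% (stated 92%).
- Bothersomeness: μ̄ = (75 × 1.1 + 38 × 1.5) / 188 = 0.742; λ = (41.29 + 9.61 + 21.83) / 5.664 = 12.84. Power is 90.0% (stated 89%).

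**Step 3: power of the planned procedure**

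The two tests share data, so their powers cannot simply be multiplied. The joint probability was simulated: 2,000,000 trials per outcome at the assumed means, pooled variance on 185 df, counting trials in which the omnibus F was significant and the yoga versus self care t-test was significant in favour of yoga.

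| Outcome | Stated | Ungated, pooled df | Gated | Stated minus gated |
|---|---|---|---|---|
| RDQ, 2.5 points | 92% | 92.4% | 89.7% | 2.3 |
| Bothersomeness, 1.5 points | 88% | 88.3% | 85.2% | 2.8 |

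The stated figures are not powers conditional on passing the gate either. Those would be 89.7 / 92.6 = 96.9% and 85.2 / 90.0 = 94.7%.

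**Step 4: dependence on the exercise mean**

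The yoga versus self care difference was held at 2.5 (RDQ) or 1.5 (bothersomeness) and the exercise mean was moved (500,000 trials each).

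| Exercise mean | Gated, RDQ | Gated, bothersomeness |
|---|---|---|
| Equal to yoga | 89.6% | 84.2% |
| A quarter of the way to self care | 86.5% | 80.5% |
| Midway | 87.3% | 81.4% |
| Three quarters of the way | 90.6% | 85.4% |
| Equal to self care | 92.2% | 87.8% |

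Only the last row comes close to the stated values, and it is not the configuration the plan assumes.

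**The case against.** The strongest reply is that nothing in section A is miscalculated or hidden. The gate is described, its own power is printed, and the pairwise figures follow a sentence that makes them conditional on it. They are tied to a stated difference rather than to the assumed pattern of means, and no single gated figure can match them because gated power depends on the third arm. Most of this stands: it is a labelling gap, not an arithmetic error, and about 90% is the answer for one configuration. But that configuration is the plan's own, used for the omnibus power in the same section, and nothing tells the reader that the gate is left out.

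It can also be said that the planned extra covariates would recover the loss. A residual variance reduction of about 7%, an assumed value that the plan does not give, would bring gated power to 91.9% and 87.8%. That is possible, but the stated figures do not rest on it.

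Three stronger readings are tempting, and the documents do not support them.

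- **That Aim 2 power is overstated.** The 98% for yoga versus exercise is openly tied to a 2.5-point difference. Gated, it is still about 98% when self care is no better than exercise (96.6% if self care lies midway). The corresponding bothersomeness figure is 95.8% gated when self care equals exercise, against 97% stated. The 80% at the expected 1.7 points is already printed, under Aim 3; gated it is about 79%.
- **That the chance of success on both aims is wrongly presented.** The plan makes no such joint claim, and its two hypotheses are separate. The gate barely affects that probability: 76.4% without it and 76.2% with it on the RDQ, 73.8% and 73.6% on bothersomeness.
- **That the trial is too small.** Gated Aim 1 power stays above 85% on both outcomes at the assumed means.

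**Conclusion.** The point holds in a limited form. The 92% and 88% given for yoga versus self care describe a test without the gate, whereas Aim 1 will be tested with it. At the plan's assumed means the design has about 90% power on the RDQ and 85% on bothersomeness, a shortfall of 2 to 3 points from the stated values. Across the exercise means tried, gated power runs from 86.5% to 92.2% (RDQ) and from 80.5% to 87.8% (bothersomeness).

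This rests on a two-sided 0.05 level, 75:75:38 evaluable, the stated standard deviations, and a single-time-point comparison adjusted for baseline, which is the basis the plan uses. The GEE model and the additional covariates were not simulated; section B says the model with all time points should not substantially influence power. The matter is minor: the stand-alone arithmetic is right, and the sample size, the analysis and the error control need no change.

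**What to change.** In section A:

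1. State the Aim 1 power as the probability that both the omnibus F-test and the yoga versus self care test are significant under the assumed means: about 90% for the RDQ and about 85% for bothersomeness.
2. Keep the existing pairwise figures if wanted, labelled as ungated two-sample powers.
3. Add a sentence saying that gated power depends on the exercise mean, with an example: on the RDQ, about 87% if exercise lies midway between yoga and self care and about 92% if it equals self care.
4. State that the tests are two-sided, if that is what was used.

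The cost is wording only. The quoted powers become slightly less favourable, and no participants are added.

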#### B. Statistical analysis

We will analyze outcomes from all follow-up time points in a single model, adjusting for possible correlation within individuals using generalized estimating equations (GEE) [55]. Because we cannot reasonably make an assumption of constant or linear group differences over time, we will include an interaction between treatment group and time point. In this case, the multivariate model that includes all time points provides very similar results to fitting separate analysis of covariance models over time and should not substantially influence statistical power.

We also plan to adjust for other baseline characteristics. Specifically, gender, age, pain traveling below the knee but not meeting the criteria for sciatica, job related activity, and Body Mass Index. In a randomized trial of this size, most baseline values and other covariates are unlikely to differ between randomized groups. However, inclusion of baseline covariates can improve the precision of the estimate and therefore increase power to detect differences.

We will use an intent-to-treat approach in all analyses, *i.e*., individuals will be analyzed by randomized group regardless of participation in any classes. This minimizes biases that often occur when participants not receiving assigned treatments are excluded from the analyses. The linear regression model (analysis of covariance) we will use is of the form:

where *Y*(*t*) is the response at follow-up time *t*, *Baseline *is the pre-randomization value of the outcome measure, *Trt *includes dummy variables for the yoga and exercise groups, *Time *is a series of dummy variables indicating the follow-up times, and *z *is a vector of covariates representing other variables being adjusted for. (Note that α_1_, α_2_, α_3_, and α_4 _are vectors.) The referent group in this model is the self care group at the first follow-up time. The models will be fitted using GEE to take into account possible correlation within individuals over time. For each follow-up time point that the omnibus *F*-test is statistically significant, we will go on to test whether there is a difference between yoga and self care to address Aim 1 and a difference between yoga and exercise to address Aim 2.

Based on similar studies on this study population we expect to have at least a 90% follow-up rate which reduces the potential for bias due to loss of follow-up. Therefore, our primary analysis will be a complete case analysis including all observed follow-up outcomes, but we will adjust for all baseline covariates that are predictive of outcome, probability of being missing, or differences between treatment groups. We will also conduct sensitivity analyses using an imputation method for non-ignorable non-response to evaluate if our results are robust in the complete case analysis [56]. We will report both results in our manuscript.

To help us further understand the benefits of yoga as a treatment for back pain, we will explore possible interactions between treatment groups and covariates. For example, we will consider interactions of the treatment group and the baseline value that would indicate the effect of treatment depends on status at baseline. We will also test for significant interactions of treatment group with other variables (*e.g*., gender) to determine if treatment differences are modified by these variables. We will use similar methods to analyze secondary outcomes including disability days and satisfaction with care.

If we find that yoga is more effective than self care or exercise we will move to Aim 3 with the goal of exploring whether the beneficial effects of yoga on our primary outcomes are mediated through certain measured variables. As mentioned in Figure 1 and Table 4, we are interested in four major classes of measures that could mediate the effects of yoga on back pain outcomes: (1) physical function, (2) cognitive appraisal, (3) affect and stress, and (4) neuroendocrine function. In the interest of parsimony, we will narrow down the number of perspective variables within the four major classes of proposed mediators by using a modification of the framework described by Baron and Kenney [57].

We will first individually regress each of the potential mediators within a major class on the treatment group. If the potential mediator is associated with the treatment group (α-level = 0.10), we will then evaluate the magnitude of the effect of the individual potential mediator by using an inverse probability weighted (IPW) modeling approach on each of the primary outcomes (i.e., RDQ score or bothersomeness score)[58]. This approach allows us to estimate the direct effect of treatment after rebalancing the treatment groups with respect to the mediator. Specifically, we will first model the probability of the treatment given the mediator using logistic regression. From this model we will obtain the estimated probabilities that each person received their observed treatment given their observed mediator value. We will then use an inverse probability of treatment weighted regression to model the primary outcomes on treatment status while adjusting for the baseline level of the outcome. Comparing the weighted to the unweighted model will allow us to estimate how much of the direct effect of treatment on the outcome can be explained by a potential mediator.

We will do this for all potential mediators in a class and rank them based on how much of the direct effect of treatment on the outcome each explains. The potential mediators within a class that explain at least 10% of the direct effect will then be put in a multiple mediator weighted regression model to assess whether the effect can be mostly explained by a single mediator in the class or if it requires multiple mediators within the class. This stepwise approach will be used to reduce the number of mediators that will be included from a given class. It will not provide estimates of the final strength of the class of mediators since this would require the assumption that classes of potential mediators are independent of one another (i.e., physical function and stress are unrelated). Assessment of the strength of mediation from each class requires that we conduct a multiple mediator analyses evaluating all classes of mediators in a single model [59].

After determining the subset of mediators to be included from each class, we will run a final multiple mediator IPW model. The application of the IPW approach, as compared to the traditional approach of adjusting for multiple mediators, allows us to more appropriately account for confounding between a mediator and the outcome both by additional mediators and by other measured variables [60]. Further we are better able to estimate the indirect effects of each mediator in a causal framework through decomposition of the total effect of treatment into indirect effects through each mediator and the direct effect after accounting for all mediators.

All time points for which there is a significant difference between yoga and self care (or exercise) will be included in the models, and we will use GEE to account for possible correlation within subjects over time.

The results of our previous study suggest that there are several possible scenarios of treatment differences we might expect to find in our proposed trial [19]. Each of these scenarios would result in a different approach to exploring mediating factors. *Scenario 1: *yoga is more effective than self care but not significantly better than exercise, which is not significantly better than self care. In this scenario, we will look for mediators that explain the mechanisms through which yoga works compared to self care, but we cannot explore whether there are different mediators for exercise and yoga if exercise is not significantly better than self care. Thus, we will not be able to determine whether there are mechanisms of healing unique to yoga compared to a "body-focused" treatment like exercise. *Scenario 2: *yoga is significantly better than both self care and exercise, and exercise may or may not be significantly better than self care. In this scenario, we will look for mediators that may explain how yoga works compared to self care and to exercise. It is possible that these mediators are different. By focusing on the yoga vs. exercise difference, we can determine which mediators are most responsible for the unique effects of yoga, which we believe will be mostly those related to increased awareness. *Scenario 3: *both yoga and exercise are better than self care but yoga is not significantly different from exercise. In this scenario, we might conclude that the beneficial effects of yoga are solely or largely due to physical exercise, and that the awareness component has no materially important effect on back pain. However, it is possible that completely different pathways mediate these beneficial effects, and we will be able to determine this through the mediator analysis. For example, the treatment effect of yoga compared to self care might be significantly reduced when a specific mediator variable (e.g., body awareness) is included in the model, with no significant change on the treatment effect of exercise compared to self care.

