Planning on seeing a health care provider other than primary care provider for low back pain		TI

Dementia	Condition would make it difficult for fully informed consent	A
Unable to read or speak English		TI

Currently using exercise classes or yoga for back pain or has used one in past year; practiced yoga for any reason within past 3 months	Possible bias due to current or recent intervention users	TI

*A = Automated visit data

*IPE = In person examination

*TI = Telephone interview

Members determined to have any of the following during the telephone or in-person screening interviews will be excluded: non-specific causes or potential causes of low back pain (i.e., sciatica, underlying systemic or visceral disease, pregnancy, spondylolisthesis, spinal stenosis, cancer or unexplained weight loss, recent vertebral fracture); current use of yoga for their back pain or a back-specific exercise class or use in the past year; contraindication for yoga or exercise (e.g., severe disk disease); characteristics complicating the interpretation of findings (i.e., involved with litigation or compensation claim for back pain, evidence of severe or progressive neurologic deficits, previous back surgery, planning to seek other treatment for back pain, unstable medical or severe psychiatric conditions, major depression as determined by a score of 10 or greater on the Patient Health Questionnaire (PHQ)-8 [23]; inability to complete the study protocol (i.e., unable to speak or read English, plan to move out of town).

Recruitment procedures

Because the study intervention involves classes, we will recruit participants in seven cohorts consisting of 30 individuals each. We plan to recruit Group Health members who have made visits to their primary care physician for low back pain and whose pain has persisted for at least three months. However, if necessary to meet our recruitment goals, we will also post flyers in the Group Health primary care clinics and advertise in Group Health's quarterly magazine. Finally, in regions with fewer Group Health members, we may advertise the study to the general population.

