### Randomization to treatment groups

After completing the baseline assessment, participants in each cohort will be randomized, in a 2:2:1 ratio, to the yoga, therapeutic exercise or self care groups. Treatment group will be automatically assigned by a computer-generated sequence of random numbers using a program that ensures that treatment allocation cannot be changed after randomization. Participants will be randomized in blocks of varying size to ensure balanced but unpredictable assignment of participants to all groups. The sequence of randomization and blocking factor will differ for each cohort. All participants will be given the saliva collection kits and instructions for collecting the baseline saliva samples. Participants randomized to the yoga or exercise classes will be given a sheet of paper with their class time, study contact information and a map showing their class location. Just prior to the first class, participants randomized to yoga or exercise will be given a reminder call of their class time. Participants randomized to the self care group will receive a book about self-management of back pain (The Back Pain Helpbook[24]).

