### Study treatments

Participants will be randomized to yoga classes, therapeutic exercise classes or receipt of a self-care book. Both the yoga and exercise interventions will consist of 12 weekly 75-minute classes supplemented by home practice. The dose of yoga in this study was chosen because it was found effective in our previous trial back pain [19]. Conceivably, the "optimal dose" of yoga could differ from the amount of yoga we will provide, but we are unaware of studies that have examined this issue. Participants will be asked to report their weekly home practice on pre-printed home practice logs. For legal and ethical reasons, all participants will continue to have access to the services normally available under their health insurance plan, regardless of the intervention they are assigned. The treatments are described below.

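### The two class-based arms are analysed and powered as if classmates were independent; with any positive class-level correlation, standard errors are too small, mainly for yoga versus exercise

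*Protocol article*

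**What the plan says.** Delivery is in groups for two arms of three. Under Study treatments: "Both the yoga and exercise interventions will consist of 12 weekly 75-minute classes supplemented by home practice". Recruitment procedures ties the cohort structure to this: "Because the study intervention involves classes, we will recruit participants in seven cohorts consisting of 30 individuals each". Under Randomization to treatment groups, "participants in each cohort will be randomized, in a 2:2:1 ratio, to the yoga, therapeutic exercise or self care groups", so individuals are randomised within cohort. The third arm is not grouped: "Participants randomized to the self care group will receive a book about self-management of back pain".

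Under Statistical issues, B. Statistical analysis, all follow-up times enter one model, "adjusting for possible correlation within individuals using generalized estimating equations (GEE". Its terms are baseline value, treatment, time, their interaction and a covariate vector. The covariates named there are gender, age, pain below the knee, job-related activity and body mass index. None refers to class, instructor or cohort.

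Under Statistical issues, A. Sample size and the detectable difference, power is calculated for 75:75:38 analysed participants: "The power calculations are based on simple comparisons of the follow-up scores at a single point in time", adjusted for baseline. No ICC or design effect is mentioned. Pairwise tests follow only if the omnibus F-test is significant.

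**The concern.** People in one class share an instructor and a group for 12 weeks, so their outcomes may be more alike than those of people in different classes. GEE with the individual as cluster is robust to correlation within a person over time, but not to correlation between classmates. If such correlation is positive, the variance of each active-arm mean is understated. Yoga versus exercise is hit hardest because both sides are clustered; in yoga versus self care only the larger arm is.

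The yoga-exercise contrast is Aim 2, and the article says that a positive answer would suggest benefits beyond physical movement. A significant result also opens the mediator analyses. If classes differ because of who taught them or how the group worked, the planned test can report part of that variation as a yoga effect.

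This is not a detail left to a later document. The article itself states the model terms, the correlation structure and the power figures.

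**Working it through.** **Inputs from the article:** 210 randomised 2:2:1; seven cohorts of 30; 10% loss; 75:75:38 analysed; baseline-adjusted SD 3.68 (RDQ) and 2.38 (bothersomeness); 0.05 level (two-sided assumed, which reproduces the stated figures).

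**Assumptions:** one class per active arm per cohort, so 84/7 = 12 randomised and m = 75/7 = 10.7 analysed per class, and 14 classes in all. The class ICC is taken as 0.01 to 0.05 because none is given.

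**Step 1: reproduce the stated power with independent participants.**
- Yoga v exercise: SE = 3.68 × √(2/75) = 0.601. At 1.7 points, Φ(1.7/0.601 − 1.96) = 80.8% (stated 80%). At 2.5 points, 98.6% (stated 98%).
- Yoga v self care: SE = 3.68 × √(1/75 + 1/38) = 0.733. At 2.5 points, 92.7% (stated 92%).
- Omnibus RDQ test, noncentral F with 2 and 185 df: 92.6% (stated 92%).
- Bothersomeness, in the order omnibus / yoga v self care / yoga v exercise at 1.5 / at 1.1: 90.0, 88.6, 97.1, 80.8% (stated 89, 88, 97, 80%).

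All eight agree within 2 points, so no allowance for clustering was built in.

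**Step 2: add clustering in the two class arms.** Design effect DE = 1 + (m − 1) × ICC = 1 + 9.7 × ICC.
- SE(yoga v exercise) = 3.68 × √(2 × DE/75)
- SE(yoga v self care) = 3.68 × √(DE/75 + 1/38)
- Power of a test using the correct SE = Φ(difference/SE − 1.96)

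| RDQ | ICC 0 | 0.01 | 0.02 | 0.05 |
|---|---|---|---|---|
| Design effect | 1.00 | 1.10 | 1.19 | 1.49 |
| SE, yoga v exercise | 0.601 | 0.629 | 0.657 | 0.732 |
| Power, yoga v exercise, 1.7 | 81% | 77% | 74% | 64% |
| Power, yoga v exercise, 2.5 | 99% | 98% | 97% | 93% |
| Power, yoga v self care, 2.5 | 93% | 92% | 91% | 89% |

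With a t reference on 12 df (14 classes − 2), power at 1.7 points is 70%, 66% and 57% at ICC 0.01, 0.02 and 0.05. With two classes per arm per cohort (about 5.4 analysed each), the normal-approximation figures are 79%, 77% and 73%.

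**Step 3: type I error of the planned test, each contrast taken alone.** 2 × [1 − Φ(1.96 × SE at ICC 0 / true SE)].
- Yoga v exercise: 6.1%, 7.3% and 10.8% at ICC 0.01, 0.02 and 0.05.
- Yoga v self care: 5.4%, 5.8% and 6.9%.

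**Step 4: add the omnibus gate.** Simulation of the gated procedure with seven classes per active arm and 75:75:38, for yoga v exercise at ICC 0.02 and 0.05:
- All three arms equal: about 4% and 6.5%.
- Both active arms 2.5 points better than self care: about 7% and 11%, because the gate is then nearly always open.

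**Step 5: cohort effects.** A simulated cohort ICC of 0.05 shared by all arms, with no class effect, gave a type I error of about 4.5%. Variation common to a whole cohort does not cause the problem.

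**The case against.** The strongest reply is that everything depends on an ICC that the article does not give, and that the design may keep it low. Instructors are trained to one protocol and monitored, home practice is daily, outcomes are individual telephone interviews by masked staff, analysis is by intention to treat whatever the attendance, and the 26-week assessment falls 14 weeks after the last class. This stands as a reason to state the error conditionally. It does not show that the ICC is zero, and it does not make the written model able to absorb a positive one.

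Several stronger readings are tempting and do not hold:
- A reader might infer that type I error certainly exceeds 5%. That needs a positive class ICC. Even then, the gate holds yoga v exercise to about 4% at ICC 0.02 if all arms are equal.
- A reader might combine 10.8% type I error with 64% power. They belong to different tests. The planned, uncorrected test would reject at 1.7 points with probability Φ((1.7 − 1.96 × 0.601)/SE), which is 79% at ICC 0.02 and 76% at 0.05.
- A reader might take the 80% at 1.7 points as the Aim 2 target. The article labels it Aim 3; for Aims 1 and 2 the target is 2.5 points, with 98% for yoga v exercise. However, 1.7 is also the yoga-exercise gap that the article assumes for its omnibus calculation, so the figure still matters.
- A reader might count season as a cause. It is shared by all arms of a cohort.
- A reader might say that every power figure is wrong. The mediator powers of 0.86 and 0.83 come without inputs and cannot be checked.

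**Conclusion.** The point holds in conditional form. The stated model and the eight primary-outcome powers treat classmates as independent. For any positive correlation within class or instructor, the standard errors are too small: for yoga v exercise by a factor of 1.09 at ICC 0.02 and 1.22 at 0.05, for yoga v self care by only 1.03 and 1.08.

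The practical consequence is therefore concentrated in the yoga-exercise contrast. Its false-positive rate can reach about 7% to 11% when both active arms work, and the stated 80% has no slack for clustering. Conclusions on yoga v self care, and power at 2.5 points, are fairly robust.

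The direction follows from the design. The size rests on the assumed ICC range and on one class per arm per cohort, which is inferred from the cohort sizes and not stated.

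**What to change.** In B. Statistical analysis, account for class clustering in the yoga and exercise arms only, treating each self-care participant as a singleton. Either a partially nested model with a random class effect in the two class arms, or GEE clustered on class, would do. Repeated measures within a person still need to be accommodated, and either choice needs a small-sample correction for about 14 classes. If an instructor teaches several classes, say whether instructor should be the cluster. Report the class ICC with the results.

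In A. Sample size and the detectable difference, state the number of classes assumed per arm and give the eight primary-outcome powers over an ICC range of 0 to 0.05.

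The cost is analysis wording and a less favourable power statement, most visibly for yoga v exercise at 1.7 points. The class variance will be imprecisely estimated from about 14 classes, and the small-sample correction costs some further power. No new patients or data are needed, since staff already take attendance at every class.
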